### Data collection tools and techniques

Data will be collected using a semistructured and pretested questionnaire. The questionnaire used to collect the data was designed by reviewing relevant literature and related national and international standards, and the focus is on educational and ecological assessment, a mother’s experience related to pregnancy, delivery and PNC, social and epidemiological assessment, behavioral and environmental assessment, general social support and social capital and health service quality components. This will be translated to an Amharic version (the local language of the study area).

The translated version was uploaded to KoBo toolbox, and an open data kit (ODK) will be used to collect data. The study will use face-to-face interviews and the data will be collected using mobile devices in front of each selected mother’s home. Completed questionnaires will be saved in the mobile devices and will be sent to the central server immediately after completing the interview. In cases where the data collectors cannot complete the questionnaires and when an internet connection cannot be accessed the completed questionnaires will be forwarded when there is an internet connection available. The data collection will be managed directly from the Jimma University server. Each data collector and supervisor has a code to make data management easy. If a study participant in either arm moves from the study area before the study is completed, they will be registered as dropouts and lost to follow-up. This trial will have two phases of data collection: baseline study (before the intervention is introduced) and end-line study (after the intervention is introduced).

### Data quality control

Training for selected data collectors and supervisors will be conducted, with the focus on making every question commonly understood. In addition, a manual explaining each and every question with its response categories has been prepared; this manual also includes sections explaining ‘how to use ODK to collect data’ with examples demonstrating the features of the application. The data collection will be conducted by midwives who hold BSc. degrees, and will be supervised by two professionals who hold MPH degrees. In addition to this, a close follow-up by the principal investigator will be done. The field data collection will be supported by the ODK in which each and every question is required to be answered, helping to avoid missing data. Range checks will also be made for selected data values. The ODK will also allow editing of the responses in front of each interviewee. Similarly, global positioning system coordinates of each and every interview will be recorded at the end of each interview which will allow graphical representation of the study site.

### Analysis plan

Data from the trial will be analyzed by an intention-to-treat analysis at both cluster and participant levels. Participants will be assigned to the cluster they were resident in at the time the trial began. The primary data analysis will take place at the cluster level. Risk ratios will be computed at the cluster level, and the results of this cluster summary will be compared using *t* tests. Primary and secondary outcomes will be compared between intervention and control groups with random effects logistic regression models, taking account of clustering/correlation. All estimates will be presented with 95% confidence intervals. STATA version 13.0 will be used to run the analysis.

### Outcome measures

Primary outcomes are the continued utilization of maternal health care service (ANC to PNC), mothers attending the fourth ANC visit, mothers delivering at health facilities assisted by skilled care providers, and mothers attending the third PNC visit at 6 weeks after delivery.

Secondary outcome measures will assess whether the trial has an effect on early initiation of ANC (initiation of ANC before 16 weeks of gestation), and utilization of the first ANC (first ANC visit attendance, regardless of the time of initiation).

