**Methods:**

A community-level, cluster-randomized controlled trial will be conducted to compare the effectiveness of checklist-based box system interventions over the routine standard of care as a control arm. The intervention will use a health-extension program provided by health extension workers and midwives using a special type of health education scheduling box placed at health posts and a service utilization monitoring box placed at health centers. For this, 1200 pregnant mothers at below 16 weeks of gestation will be recruited from 30 clusters. Suspected pregnant mothers will be identified through a community survey and linked to the nearby health center. With effective communication between health centers and health posts, dropout-tracing mechanisms are implemented to help mothers resume service utilization. Data will be collected using an open data kit and analyzed using STATA version 13.0. Data will be analyzed by the intention-to-treat analysis. Risk ratios will be computed at the cluster level and the summary will be compared using *t* tests. Outcomes between intervention and control groups will be compared with random effects logistic regression models. Achieving four antenatal care visits, health facility delivery, and postnatal care visits at 6 weeks after delivery were treated as primary outcomes for this study.

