### Participant eligibility criteria

The participants for this trial will be pregnant mothers residing in three of the selected districts of East Gojjam zone (Debre-Markos, Gozamin and Machakel districts). Recruitment will pass a two-stage screening process. Using a preset criterion, the initial screening will be done at the community level using the pregnancy screening checklist from Stanback et al [18]. (last menstrual period for gestational age dating), and mothers having a suspected pregnancy will have a laboratory confirmation at the health center. Those having a gestational age of 16 weeks will be recruited for the study. Mothers who fulfill the above criteria but who have severe psychological illness which could interfere with consent and study participation, those who have severe clinical complications that need hospitalization and mothers who need a special type of ANC follow-up, other than the recommended focused ANC, will be excluded from the study.

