### Screening and enrollment

In Ethiopia, the linkage between primary health care units is defined and each health post has its own catchment population to serve. This linkage works primarily by proximity of health facilities to the catchment population. Community-level referral of this trial works following this defined primary health care unit linkage. Based on this, HEWs will use a family folder (a detailed record about households) to identify women of reproductive age. The first-level screening will then take place at the community level using the pregnancy screening checklist of Stanback et al. [18]. Mothers having suspected pregnancy will receive a community-level referral slip for them to be received by the nearby health center. The second screening will take place at the health center using a beta-human chorionic gonadotropin (HCG) urine test as laboratory confirmation of pregnancy. Mothers who have known pregnancy but have not initiated the first ANC will also be referred for the service. If a mother has a positive HCG result, she will be recruited for the study and on the same day she will receive the first ANC service.

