##### Health center

Once the mothers are linked to a nearby health center, they will be followed for their subsequent attendance of consecutive maternal health care services of ANC (second to fourth visits), skilled birth attendance, and PNC (1–3 visits). This will be checked using a specially designed service utilization monitoring box. This box is a nine-compartment box (Fig. 3); the first compartment is for mothers suspected of being pregnancy using the pregnancy screening checklist from the HEWs. If the mothers arrive and confirm their pregnancy (via HCG test) they will receive the first ANC and their card will be transferred to the next compartment; the same procedure will be followed for the coming consecutive maternal health care service visits. The visits for ANC will follow the four-visit WHO ANC model (i.e., first ANC before 16 weeks of gestation, second ANC at 24–28 weeks, third ANC at 30–32 weeks, fourth ANC at 36–40 weeks); facility delivery is that assisted by skilled health-care providers at the health-center level and above; and visits for PNC are PNC visit 1 at 6 h, PNC visit 2 at 6 days and PNC visit 3 at 6 weeks after delivery. This service utilization monitoring box will help midwives identify mothers who fail to follow the above smooth transition. If a mother is identified as a ‘dropout’, midwives at health centers will communicate to HEWs in the area in which the mother lives. Again, these mothers will be approached for person-centered health education to resume their service within the recommended time interval.

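### Women are enrolled on the day of their first ANC visit and before 16 weeks, so among women enrolled that way both secondary outcomes are 100% by construction and cannot show an intervention effect

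*Protocol article*

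**What the plan says.** All references are to the protocol article.

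- **Outcome measures.** The secondary outcomes are "early initiation of ANC (initiation of ANC before 16 weeks of gestation), and utilization of the first ANC". The second is defined as "first ANC visit attendance, regardless of the time of initiation".
- **Screening and enrollment.** A woman is referred from community screening to the health center and tested there. If the test is positive, "she will be recruited for the study and on the same day she will receive the first ANC service". Women already known to be pregnant are covered too: "Mothers who have known pregnancy but have not initiated the first ANC will also be referred for the service".
- **Gestational age.** The abstract says "1200 pregnant mothers at below 16 weeks of gestation will be recruited from 30 clusters". The eligibility section says "Those having a gestational age of 16 weeks will be recruited for the study". The enrolment section repeats no limit. The visit schedule under Health center has "first ANC before 16 weeks of gestation".
- **Control.** Control clusters get neither community pregnancy screening nor the boxes. No separate enrolment route is described for them.
- **Analysis plan.** Primary and secondary outcomes are compared between arms with random effects logistic regression, alongside cluster-level risk ratios and t tests.
- **Randomization and sampling procedures; Data collection.** The baseline is a random sample of women who delivered in the preceding year. An end-line phase is planned, but its sampling frame is not given.

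**The concern.** An outcome can be compared between arms only if the women in the denominator could have gone either way. Here the step that makes a woman a participant is also the event that the secondary outcomes count. Women who never attend ANC do not enter the cohort, and under the abstract's limit neither do women who start late.

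This matters because entry to ANC is where community pregnancy identification should act most directly. The Background motivates the trial partly by late first visits, and the Discussion presents community identification as the departure from routine care. As written, the trial would report two secondary comparisons on that question that are either not estimable or produced by the enrolment process.

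**Working it through.** The article gives no expected rate or effect size for the secondary outcomes, so there is no stated figure to reproduce. The sample size rests on third PNC. The check is mainly one of logic.

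**Step 1: first ANC use.** By the enrolment section, recruitment and first ANC fall on the same day, so P(first ANC = 1 | enrolled by this route) = 1.

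**Step 2: start before 16 weeks.** With the abstract's limit and a same-day first visit, gestation at first ANC equals gestation at recruitment, which is below 16 weeks. So P(start before 16 weeks | enrolled by this route) = 1.

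**Step 3: both arms enter by this rule (assumption A).** Each arm of 600 has proportion 1.
- Difference = 1 − 1 = 0, and risk ratio = 1/1 = 1.
- Variance of each proportion = 1 × (1 − 1) = 0, so the standard error is 0 with any design effect.
- The cluster-level t statistic is 0/0, which is undefined.
- With no non-events, the log odds are infinite in both arms and no odds ratio is estimable.

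**Step 4: control women enter another way (assumption B).** The intervention arm stays at 1 by construction. If a proportion c of control women have the outcome, the difference is 1 − c and the risk ratio is 1/c, whatever the intervention does. For first ANC use:

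| c in controls (assumed) | Difference | Risk ratio |
|---|---|---|
| 100% | 0 points | 1.00 |
| 67.1% (regional survey figure, Setting) | 32.9 points | 1/0.671 = 1.49 |

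The second row is an illustration, not a forecast. It shows how large a gap enrolment alone could create.

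**Step 5: would the outcomes be informative in another denominator?** Take 40 women per cluster and 15 clusters per arm, and assume that the article's intracluster correlation of 0.04849 and its 12-point effect also apply here.
- Design effect = 1 + 39 × 0.04849 = 2.891.
- Effective sample per arm = 600/2.891 = 207.5.
- Power (two-sided 5%, normal approximation) is about 0.79 for first ANC, 67.1% to 79.1%.
- Power is about 0.75 for early start, 26.2% to 38.2%.

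The 26.2% is only a rough stand-in: it is a national figure for first-trimester start among ANC attenders, not start before 16 weeks among all women. On these assumptions, a catchment sample of the planned size would carry useful information.

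**The case against.** The strongest reply is that the article may intend a population comparison. The sampling section says that previously delivered women also serve for comparing utilization after the intervention, an end-line phase is planned, and counting a first visit at any time makes sense only if late starters are in the denominator. This has some force: the end-line denominator is unclear. But the only population sample described covers births before the intervention. The trial is sized on recruited pregnant women, and nowhere are the secondary outcomes given a different denominator. The monitoring box does hold suspected pregnancies before confirmation, but only in the intervention arm, so it cannot supply a common denominator.

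A second reply is that the enrolment section states no gestational limit, so early start could vary. Read alone, that is so. But that reading sets aside the abstract's limit, and first ANC use would still be constant.

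Some stronger readings are tempting but unsupported:
- **That the outcomes cannot differ, at 600/600 in each arm.** This applies the described route to control women. That route begins with community screening, which the control arm does not receive.
- **That early start would be 0% in both arms.** This takes the eligibility section's "Those having a gestational age of 16 weeks will be recruited for the study" literally. The abstract, visit schedule and outcome definition all speak of below or before 16 weeks, so a dropped word is the likelier explanation.
- **That sites are admitting different women.** Nothing in the article shows this.

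**Conclusion.** The point holds for both listed secondary outcomes. Among women enrolled by the described route, each is 100% by construction: first ANC use on the enrolment section alone, early start when the abstract's limit is added. If control women follow the same rule, the comparison has no variance and cannot be estimated. If they do not, the comparison is confounded by enrolment route. Neither case yields an intervention effect. This is a conflict between a stated enrolment rule and stated outcomes, not a detail left to an analysis plan.

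A reader might infer that the trial's main question is compromised. The article does not support that: continued utilization, fourth ANC visit, facility delivery and third PNC visit are not made constant by this rule, and the sample size does not depend on the secondary outcomes. The defect is worth correcting, but it is confined to the secondary objectives. The gestational-age discrepancy is a matter of wording.

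**What to change.** Do not compare these two outcomes among enrolled women. There are two ways to do this:

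1. **Drop them as comparative outcomes.** This costs almost nothing beyond the wording of the outcome and analysis sections, but the question about ANC entry then goes unanswered.
2. **Measure them at the planned end-line** among all women who gave birth in each catchment during follow-up, whether or not they were enrolled, listed and sampled identically in both arms with the method used for the baseline sample. Women who never attended ANC must be included. The baseline list cannot be reused because it covers earlier births, so this needs a new listing, a new sample and the fieldwork for both. A question on the timing of first ANC may also be needed, since the article lists questionnaire themes and not items.

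Under either option, reconcile the gestational-age wording of the eligibility section with that of the abstract, and carry the same limit into the enrolment section. That is a text edit.

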### Dissemination plan

A detailed study protocol will be published in an open-access journal. Any modifications made to the protocol will be communicated to relevant parties, such as the trial registry and both of the ethics committees. After the results are produced they will be submitted to the Jimma University, the Amhara Region Public Health Institute, the East Gojjam zone Health Department, and governmental and nongovernmental organizations working in maternal health programs. The findings of this study will also be presented in scientific conferences. Also, a manuscript will be prepared and submitted to a peer-reviewed scientific journal for possible publication.

## Discussion

This trial is designed to improve continued utilization of maternal health care services and will be applied both in urban and rural settings. Unlike routine care, pregnancy identification will take place at the community level. As this trial is designed to be implemented by combining both demand-creation and service utilization monitoring components, the investigators believe that the evidence generated will contribute to maternal health programs at the regional and national level (Additional files 1 and 2, Table 1).

## Trial status

Thirty clusters have been selected and the preparatory activities such as development of training manuals, referral slips and registers are completed. A sensitization workshop for local health administrators and training for intervention implementers (HEWs and midwives) has been conducted. The specification for specially designed boxes for health posts and health centers has been developed and procurement and distribution has been made accordingly. The baseline study has collected data in both the intervention and control clusters, and enrollment of mothers as per the criterion is being conducted. This is protocol version 1, dated 26 March 2019. Recruitment began on 22 November 2018, and the approximate date of recruitment completion is October 2019.

## Data Availability

Not applicable.

## Abbreviations

ANC: Antenatal Care
CBBSI: Checklist-based box system intervention
HCG: Human chorionic gonadotropin
HEW: Health extension worker
ODK: Open-data kit
PNC: Postnatal care
WHO: World Health Organization
